## Statistical analysis

Feasibility data will be analysed using descriptive statistics. All data analysis will be undertaken blind to allocation. The following will be reported, using the data obtained from the OptiBreech mTC Database:

- Recruitment rate recorded as the number of eligible participants who consent to participate in the study by 6 months (randomised) and overall (non-randomised);
- Acceptance rate recorded as the number of participants randomised to OptiBreech Care who plan a vaginal breech birth, and the number of participants randomised to the control who attempt an ECV;
- Attrition rate recorded as the number of participants who consent to participate who remain in the study until the end of follow-up at 4 months after birth;
- Long-term attrition rate recorded as the number of OptiBreech 1 participants who complete 1-year and 2-year follow-up surveys when invited;
- Fidelity to intervention recorded as number of planned VBBs attended by a proficient team member;
- Costs to deliver the service recorded as total number of days and nights spent on call to support planned VBBs in the trial by 6 months;
- Neonatal admission rates according to intention to treat in the trial and actual mode of birth;
- Mode of birth by intention to treat (care pathway) and intended mode of birth;
- All severe adverse neonatal and maternal outcomes by intention to treat, intended mode of birth and actual mode of birth.

In a future trial ‘intention to treat’ will make reference to the flow of women/birthing people through the breech care pathway as depicted in Figure 4 below.

Figure 4: Flow of women/birthing people through the breech care pathway

Potential primary outcomes for a trial could be:

**Randomised to ‘offer ECV’ vs ‘offer OptiBreech care’ (orange)**

1. Potential primary outcome = neonatal admission. In the latest Cochrane Review,^37^ neonatal admission occurs 121/1000 following ECV.
2. Potential secondary outcome = Mode of birth. In the latest Cochrane Review,^37^ CS rate is 180/1000 following ECV.

**Cohort analysis**

Potential primary outcome = composite perinatal death or serious morbidity (maternal and neonatal) following enrolment

1. Groups 1: ECV (grey) versus planned VBB with no ECV (dark green). Cochrane review: Incidence of Apgar <7 at 5 minutes, 44/1000 following ECV, 70/1000 following no ECV, considered equivalent.
2. Groups 2: VBB with OptiBreech care (planned and unplanned) versus VBB without OptiBreech care (planned and unplanned) (all green, subgroups). In the Term Breech Trial,^45^ this rate was 5%. In the PREMODA cohort study,^71^ it was 1.6%.
3. Additional comparisons: all planned CS (all blue) vs all planned cephalic birth after ECV (yellow) vs VBB with OptiBreech care vs VBB without OptiBreech care (all green)
   1. Planned cephalic birth after ECV as control

Potential secondary outcome = mode of birth

1. Comparison: ECV attempted (grey) versus planned VBB with no ECV (dark green)
2. Comparison: VBB with OptiBreech team versus no OptiBreech team present (all green, subgroups)

We will report on incidence rates for all of these outcomes that may be used as comparators.

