## Review of existing evidence

The Cochrane Review on ‘Planned caesarean section for term breech delivery’ reports short-term benefits for infants with no short-term differences for mothers and no long-term differences for children when planned CS is compared to planned breech birth (risk ratios outlined above).^15^ The review includes three trials. Each of these were conducted prior to 2000, none of them include physiological breech birth (PBB) methods,^38^ and none of them includes a care pathway intervention specifically designed to improve the safety of vaginal breech birth. The review concludes by recommending research on strategies to improve the safety of vaginal breech delivery. In a secondary analysis of the largest trial, the presence of an experienced midwife or obstetrician was the only intervention demonstrated to lower risks associated with vaginal breech birth (OR: 0.30, 95% CI, 0.13-0.68, *p*=.004).^39^

The Cochrane Review on ‘External cephalic version for breech presentation at term’ reports benefits for mothers with no significant differences for infants when ECV is compared with no ECV.^37^ In this review, ECV reduces the CS rate compared to no ECV (RR 0.57, 95% CI 0.40 to 0.82, evidence graded very low). The review found no significant differences in neonatal outcomes, including the incidence of Apgar score ratings below seven at one minute or five minutes, low umbilical vein pH levels, neonatal admission, and perinatal death.

In a large UK cohort study, ECV was associated with a combined stillbirth and neonatal mortality rate of 1.9 per 1000,^40^ including all subsequent modes of delivery: cephalic births, breech births and CS. A population-level cohort study in the Netherlands associated planned vaginal breech birth with a perinatal mortality rate of 1.6 per 1000, and 1.3 per 1000 when cases undiagnosed before labour were excluded.^41^ Also in the Netherlands during the same period, a large series reported a perinatal mortality rate of 1.8 per 1000 following ECV.^42^ These figures suggest near parity in neonatal outcomes between cephalic birth following ECV and breech birth.

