In order to proceed with a vaginal breech delivery as part of the OptiBreech trial, it is mandatory for one fully proficient OptiBreech Team member to be present throughout the active second stage (i.e. from starting pushing, to completion of delivery), to offer support and maintain situational awareness. Hands-on clinical care should be provided by someone who has received physiological breech birth training as described above, either through completion of the OptiBreech training package or as part of annual mandatory training activities. If this level of training and experience is not available, the situation must be escalated to the on-call consultant to decide whether to discuss with the woman, whether a standard vaginal breech delivery can be considered or alternatively, whether delivery by caesarean section is required.

Ability to have a proficient team member attend 90% of planned vaginal breech births is a criterion for entering the randomisation component of this study. This will be confirmed either through participation in OptiBreech 1 or through enrolment of women requesting a VBB in the observational cohort study.

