# Data

## Data to be collected

The data we aim to collect is influenced by the following factors:

1. Our systematic review of outcomes reported in effectiveness studies of breech birth at term;^54^
2. The views of our PPI group members about what outcomes are important to women but under-reported or not reported at all;^54^
3. The need to pilot data collection on all endpoints that may be used in a substantive trial; and
4. Our intention to determine and eventually compare the factors that impact cost effectiveness in the control and intervention pathways.

We have listed all dates and times as ‘date’ in data type, although our intention is to calculate time-to-event intervals where relevant. Depending on the woman’s care pathway and personal choices, not all categories of data will require completion (e.g. ECV, induction, labour care). Additionally, almost all of the data points would be routinely collected during thorough contemporaneous documentation. We have outlined the data we need in order to understand how these variables interact within the care pathways.

| Baseline data | | | | | |
| --- | --- | --- | --- | --- | --- |
|  | Source  N = electronic or handheld record  P = participant  A = procedure | Why  * = explanatory | Standardised tool or procedure | Form of data | |
| Estimated date of birth | A | * | USS or patient-reported dates | date | |
| By menstrual dates or ultrasound | N | explanatory |  | binary | |
| Point of diagnosis | N | eligibility |  | binary | |
| Referred by? | N | * |  | categorical | |
| Name | P | Follow-up |  |  | |
| Date of Birth | P | * |  | date | |
| Contact details | P | Follow-up |  |  | |
| NHS Number and Medical Record Number | N | Follow-up |  | ID | |
| PAS General Practitioner ID | N | Follow-up |  | ID | |
| Post Code | P | * |  |  | |
| Gender | P | * |  | categorical | |
| Ethnicity | P | * |  | categorical | |
| First language spoken | P | * |  | categorical | |
| Interpreter required? | P |  |  |  |  |
| Highest level of education | P | * |  | categorical | |
| Baby feeding plans | P | * |  | categorical | |
| Planned place of birth prior to diagnosis | P | * |  | categorical | |
| Parity | N | * |  | categorical | |
| Height and Weight at booking | A | * | Routine | continuous | |
| Rhesus status | A | * | Routine blood test | binary | |
| Previous pregnancy complications | N | * |  | categorical | |
| Maternal concerns, including uterine anomalies | N | * |  | categorical | |

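### The with/without OptiBreech comparison pools planned and unplanned vaginal breech births, so its rates are confounded by planned status and may show a spurious benefit

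*Protocol*

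**What the plan says.** Protocol chapter 13, Cohort analysis, names the outcome: "Potential primary outcome = composite perinatal death or serious morbidity (maternal and neonatal) following enrolment". The second comparison listed for it, Groups 2, is "VBB with OptiBreech care (planned and unplanned) versus VBB without OptiBreech care (planned and unplanned"), with a bracketed note that reads all green, subgroups. The colours refer to Figure 4, which is not available in the text. A secondary comparison, for mode of birth, sets births with the OptiBreech team against births without it, again with no mention of planning. The section ends: "We will report on incidence rates for all of these outcomes that may be used as comparators".

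Three other places bear on the point:
- **Attendance.** Under Proficiency criteria (chapter 9): "Ability to have a proficient team member attend 90% of planned vaginal breech births is a criterion" for entering the randomised part. Counselling and Attendance in labour (chapter 9) describe caseloading by the team and local arrangements for calling it to women under OptiBreech care. Breech presentation diagnosed in Labour (chapter 8) brings unplanned births into the cohort whether or not a team member attended.
- **Risk.** Review of existing evidence (chapter 4) cites a perinatal mortality of 1.6 per 1000 in a national cohort, and "1.3 per 1000 when cases undiagnosed before labour were excluded". The introduction adds that all but one of the reviewed cerebral palsy claims from vaginal breech birth were unexpected breech births.
- **Other breakdowns.** Statistical analysis (chapter 13) reports severe outcomes by allocation, by intended mode of birth and by actual mode of birth. It does not cross these with OptiBreech attendance.

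**The concern.** A crude comparison by attendance is confounded by planned status when two conditions hold: attendance depends on whether the birth was planned, and planned status affects risk. The Protocol gives grounds for both. The group with OptiBreech care would then hold a larger share of planned births than the group without it. Part of any difference in rates would reflect late detection of the breech, not the care given.

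The comparison listed just before this one restricts its vaginal-birth group to planned births, so the Protocol draws the distinction there and drops it here. The secondary team-present versus team-absent comparison has the same weakness.

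What is at stake is the next study. Incidence rates from this pilot are meant to inform its power calculations and choice of comparators. A spuriously favourable difference could be carried into that design or into counselling.

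**Working it through.** The Protocol gives no effect size, power or expected rates by attendance for this comparison, so there is no stated figure to reproduce. The check asks what the pooled comparison would show if OptiBreech care had no effect.

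**Inputs**
- Perinatal mortality 1.6 per 1000 overall and 1.3 per 1000 without undiagnosed cases (Review of existing evidence).
- Share of breech presentations first found in labour: 20-30% (Breech presentation diagnosed in Labour). It is used as an assumption for *f*, the undiagnosed share in the cited cohort, and for *s*, the unplanned share of vaginal breech births here. The Protocol gives neither.
- Share of planned births attended by the team, *ap*: 90% (the entry criterion), or 75% from the 9/12 with a proficient attendant in Table 2. That 9/12 is not reported by planned status, so 75% is an assumption for planned births.
- Share of unplanned births attended, *au*: not given; 0-75% is assumed.

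**Step 1: risk ratio, undiagnosed to diagnosed.** Solve 1.6 = (1 - f) × 1.3 + f × m for m.
- f = 0.20: m = (1.6 - 1.04)/0.20 = 2.8 per 1000; r = 2.8/1.3 = 2.15.
- f = 0.30: m = (1.6 - 0.91)/0.30 = 2.3 per 1000; r = 2.3/1.3 = 1.77.

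**Step 2: planned share in each group.**
- With care: P1 = (1 - s)·ap / [(1 - s)·ap + s·au].
- Without care: P0 = (1 - s)(1 - ap) / [(1 - s)(1 - ap) + s(1 - au)].

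**Step 3: pooled ratio under no effect.** RR = [P1 + (1 - P1)·r] / [P0 + (1 - P0)·r].

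*Example:* s = 0.20, ap = 0.90, au = 0.25, r = 2.15.
- P1 = 0.72/(0.72 + 0.05) = 0.935.
- P0 = 0.08/(0.08 + 0.15) = 0.348.
- RR = (0.935 + 0.065 × 2.15)/(0.348 + 0.652 × 2.15) = 1.075/1.750 = 0.61.

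**Results** (s = 20-30%, r = 1.77-2.15, no true effect):

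| Planned births attended | Unplanned births attended | Planned share with care | Planned share without care | Pooled ratio |
|---|---|---|---|---|
| 90% | 0% | 100% | 19-29% | 0.52-0.65 |
| 90% | 25% | 89-94% | 24-35% | 0.60-0.70 |
| 90% | 50% | 81-88% | 32-44% | 0.68-0.77 |
| 90% | 75% | 74-83% | 48-62% | 0.82-0.87 |
| 75% | 0% | 100% | 37-50% | 0.58-0.72 |
| 75% | 25% | 88-92% | 44-57% | 0.69-0.80 |
| 75% | 50% | 78-86% | 54-67% | 0.82-0.88 |
| 75% | 75% | 70-80% | 70-80% | 1.00 |

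Within planned births, and within unplanned births, the ratio is 1.00 in every row by construction. The whole departure from 1 comes from pooling. It vanishes if both kinds of birth are attended equally often or carry equal risk.

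**The case against.** **Status of the comparison.** The list is introduced as possible outcomes for a future trial. This study promises descriptive incidence rates, claims no power for safety and promises no ratio. The feasibility formula and the figure of 2280 women do not use this comparison. All of this stands, and it limits the consequence.

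**The word subgroups.** It may mean that planned and unplanned births are to be shown separately. Without Figure 4 this cannot be settled. The secondary comparison uses the same word for team present versus absent, so it need not mean a split by planning. The ambiguity stands and is itself a reason to state the split.

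**Existing safeguard.** Reporting by intended mode of birth separates outcomes by plan, but not by plan and attendance together. It helps only in part.

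**Weakness of the illustration.** The mortality ratio may not carry over to a composite that includes morbidity. The 20-30% concerns sites without routine third-trimester scans, not the cited cohort. That cohort is itself described as planned vaginal breech birth, so its two rates are not a clean planned/unplanned split. The introduction also attributes some of the risk of unexpected births to lost skills, so part of the excess may be an effect of attendance itself. The litigation figure has no denominator. These points weaken the size, not the direction.

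**A stronger reading.** A reader might infer that the comparison is mostly planned against unexpected births and will show a large false benefit. The documents do not support that. They give neither the share of unplanned births attended nor the number of planned births without the team. Some of the latter are expected, since women in standard care who choose a vaginal breech birth are looked after by staff on duty unless they are referred for OptiBreech care.

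**Conclusion.** The point holds in a limited form. As written, the comparison pools planned and unplanned births on both sides, and no readable text separates them by attendance. The pooled rates are confounded by planned status and may show a benefit of OptiBreech care where none exists.

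Under no effect, the pooled ratio is about 0.5 to 1.0. It is near the lower end only if about 90% of planned births and few unplanned births are attended, and it is 1.00 if both are attended equally often. This rests on an assumed 20-30% unplanned share, assumed attendance of unplanned births, and a risk ratio of 1.77-2.15 derived from mortality.

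Because the comparison is descriptive here and only a candidate for a later trial, this is a correction to reporting. It does not threaten the feasibility conclusions.

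**What to change.** Replace the pooled comparison, and the matching secondary one, with a four-cell table: planned or unplanned, with or without OptiBreech care. Give the count and denominator in each cell. Compare only within planned births and within unplanned births, and state that pooled rates are not to be read as an effect of care. Say what the subgroups label means.

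Define planned status from the recorded plan for mode of birth together with "Point of diagnosis". Point of diagnosis alone is not enough: a woman with a known breech who planned a caesarean and then gave birth vaginally is diagnosed but unplanned. The initial plan after counselling, the point of diagnosis and the presence of a proficient attendant are all already on the data collection list.

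The cost is a table layout and one definition. The downside is small cells. As a rough guide, if 13/27 of 154 women gave birth vaginally (the Table 2 proportion, an assumption here), there would be about 74 births (154 × 13/27). At the 5% and 1.6% reference rates quoted for this comparison, that is about 3.7 and 1.2 events in all. The within-stratum comparisons will therefore be descriptive only. Pooling would not cure this, because the total number of events is just as small.

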## Secondary Outcomes

The following potential primary and secondary outcomes for a substantive trial will be feasibility-tested, and incidence rates will be used to inform power calculations for the substantive trial.

1. Admission to higher-level neonatal care, measured at 28 days following birth, as a binary (yes/no) and continuous (number of days/nights) outcome, from patients’ medical records;
2. Mode of birth measured using patient’s medical records on day of birth, as a categorial measurement to include the following categories: vaginal breech birth, forceps breech, pre-labour CS, emergency CS, cephalic vaginal birth, cephalic forceps, cephalic ventouse;
3. Composite neonatal perinatal death or serious adverse morbidity, measured at 28 days following birth, from patients’ medical notes; serious neonatal morbidity to include the following: 5 minute APGAR score <7, peripheral nerve injury present at discharge from hospital, skull fracture, spinal cord injury, admission to NICU>4 days, intubation/ventilation >24 hours, convulsions >24 hours, parenteral or tube feeding >24 hours;
4. Composite maternal death or serious morbidity, measured at 28 days following birth, from patients’ medical notes; serious maternal morbidity to include the following: postpartum haemorrhage >1000 mL, obstetric anal sphincter injury, cervical laceration involving lower uterine segment, vertical uterine incision or serious extension to transverse uterine incision, bladder, ureter or bowel injury requiring repair, dilation and curettage for bleeding or retained placental tissue, manual removal of placenta, uterine rupture, hysterectomy, vulval or perineal haematoma requiring evacuation, wound dehiscence / breakdown, wound infection requiring prolonged hospital stay / readmission / antibiotics, sepsis, disseminated intravascular coagulation;
5. Use of services following referral for breech care, to include antenatal and postnatal appointments, total time spent admitted to hospital, number of ECVs, number of ultrasound scans, and professionals present at birth, measured at 28 days following birth from patients’ medical notes;
6. Satisfaction with care, measured using previously validated survey questions with a 5-point Likert scale, at 1 month post birth
7. Experience of childbirth, measured using the ‘Childbirth Experience Questionnaire’^59,60^ at 1 month post birth

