The OptiBreech team members should communicate clearly and often with the clinical team on duty, especially if difficulty is anticipated. The on-duty consultant obstetrician or senior obstetric registrar is encouraged but not required to be in the room at the time of the birth, in order to facilitate closer teamwork in case complications or difficulties arise. If the OptiBreech team member feels that either forceps (for midwives) or a CS is necessary, the OptiBreech team member should clearly state their recommendation to the woman and the senior obstetrician on duty. They should also state clearly to both parties that they are handing over care and document this in the notes. They may stay to assist the clinical team if all agree this is helpful, but it is not required. In cases where the OptiBreech lead has recommended a CS and the woman or other staff decline, this is recorded in the CRF.

OptiBreech clinical responsibility will finish when care is handed over or the birth is complete, with the birthing person and neonate stabilised. On-duty labour ward staff should provide all standard follow-up care, including suturing, unless otherwise agreed.

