| Planned mode of birth following this ECV attempt | N | * |  | categorical |
| Induction of Labour | | | | |
| Number of cervical sweeps | A | * | Routine / chosen procedure | ordinal |
| Date | N | * |  | date |
| Other methods of induction used | N | * |  | categorical |
| Date/time admitted for induction of labour | N | * |  | date |
| Methods used | A | * | Routine / chosen procedure | categorical |
| Labour Care | | | | |
| Date/time admitted | N | * |  | date |
| Initial place of care | N | * |  | categorical |
| Vaginal examination – dates and time | A | * | Routine / chosen procedure | date |
| Dilatation and station | N | * |  | ordinal |
| Type of fetal monitoring used in first stage | A | * | Routine / chosen procedure | categorical |
| Meconium-stained liquor in first stage of labour | N | * |  | binary |
| Oxytocin infusion started AFTER the onset of active labour? | A | * | Drug administration | binary |
| Time | N | * |  | date |
| Was oxytocin infusion started AFTER the onset of active labour | N | * |  | binary |
| Was an amniotomy performed AFTER the onset of active labour? | A | * | Routine / chosen procedure | binary |
| Analgesia / Anaesthetic | A | * | Drug administration | categorical |
| Date/time second stage of labour started | N | * |  | date |
| Date of start of expulsive pushing effort | N | * |  | date |
| Type of fetal monitoring used for second stage | A | * | Routine / chosen procedure | categorical |
| Maternal birthing position | N | * |  | categorical |
| Lead attendant | N | * |  | categorical |
| Continuity of carer | N | outcome |  | binary |
| Cord prolapse | N | * |  | categorical, date |
| Placental abruption | N | * |  | Categorical, date |
| Time of onset of spontaneous respirations | N | * |  | date |
| Vaginal breech births only | | | | |
| Experience level of lead attendant | N | * |  | categorical |
| Had professional attended OptiBreech training? | N | * |  | binary |
| Professional who met OptiBreech proficiency criteria? | N | * |  | binary |
| Presenting part first seen | N | * |  | date |
| Time first visible | N | * |  | date |
| Anterior buttock first visible | N | * |  | date |
| Was the birth filmed | N | * |  | binary |
| Maternal position at start of emergence | N | * |  | categorical |
| Both buttocks/anus visible on perineum between contractions | N | fidelity |  | date |
| Position of fetal pelvis at emergence | N | * |  | categorical |
| Pelvis born | N | * |  | date |

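### The cohort comparison of mode of birth with and without the OptiBreech team defines its groups by the outcome, so its caesarean contrast is either zero by definition or biased towards the team

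*Protocol*

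**What the plan says.** Section 13, Statistical analysis, ends with a list of outcomes and comparisons that a future trial might use. Under Cohort analysis it gives "Potential secondary outcome = mode of birth" with two comparisons. The first is defined by exposure and plan: "Comparison: ECV attempted (grey) versus planned VBB with no ECV (dark green". The second is "Comparison: VBB with OptiBreech team versus no OptiBreech team present (all green, subgroups". Higher in the same list, a comparison carrying the same green label is spelled out as "VBB with OptiBreech care (planned and unplanned) versus VBB without OptiBreech care (planned and unplanned". The list closes: "We will report on incidence rates for all of these outcomes that may be used as comparators".

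Section 5, Secondary Outcomes, item 2, gives the categories of mode of birth: "vaginal breech birth, forceps breech, pre-labour CS, emergency CS, cephalic vaginal birth, cephalic forceps, cephalic ventouse". That section also says incidence rates will inform power calculations for the substantive trial.

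Team attendance is described in several places:
- Section 9, Proficiency criteria: a proficient member must be present in the active second stage.
- Section 9, Attendance in labour and clinical responsibility: the team is involved from the first labour assessment, though not necessarily in person. Once forceps (for midwives) or caesarean is thought necessary, care is handed over. On staying afterwards: "They may stay to assist the clinical team if all agree this is helpful, but it is not required".
- Section 11, Protocol compliance: the fidelity criterion is team presence at vaginal breech births.
- Section 12, Data to be collected: the item "Professional who met OptiBreech proficiency criteria" stands under the heading for vaginal breech births only.

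**The concern.** In a comparison of mode of birth, group membership should be settled before the mode of birth is known. Here both group labels contain a mode of birth, and the word planned, which the first comparison has, is missing. The split is then by team presence, which the protocol requires, and records with proficiency, mainly where the labour reaches a vaginal breech birth.

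The section on the randomised contrast illustrates mode of birth by its caesarean rate, so caesarean is the quantity a reader will look for. On one reading the comparison cannot show it. On the other it can show more vaginal births with the team when the team has no effect. The figures are meant to help plan a larger study, and a larger cohort would make the same artefact look more certain.

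**Working it through.** **Inputs, from Table 2 (OptiBreech 1).** Of 27 women there were 13 vaginal births, 5 pre-labour caesareans and 9 in-labour caesareans; 13 + 5 + 9 = 27. One baby turned head-down before labour. A fully proficient person was present at 9 of 12, and 9/12 = 75%, as the table states.

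**Assumption.** The 12 are the actual vaginal breech births, that is, 13 vaginal births less the one baby that turned. The table does not say so. The same denominator serves for the pelvis-to-head interval, which fits.

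**Reading A: VBB is an actual vaginal breech birth.** An unplanned one can only be an actual one, so the fuller description of the green groups points this way. Five of the seven mode categories cannot then occur. Caesarean is 0/9 with the team and 0/3 without. Only vaginal breech versus forceps breech is free to vary.

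**Reading B: VBB is a planned vaginal breech birth, split by team presence.** Women with caesareans now belong in the comparison but have no entry on the proficiency item.
- If they are left missing they drop out, and Reading A returns.
- If all in-labour caesareans are counted as not attended, vaginal birth is 9/9 = 100% with the team and 3/(3 + 9) = 3/12 = 25% without. This is the extreme case.

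**Between the extremes, with no true effect.** Take the 21 labouring women (12 vaginal breech births, 9 caesareans). Suppose the team is available to 75% of them whatever the outcome: 0.75 × 12 = 9 vaginal births and 0.75 × 9 = 6.75 caesareans. Let s be the share of those 6.75 at which presence is counted.

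Caesarean rate with team = 6.75s / (9 + 6.75s)

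Caesarean rate without team = (9 − 6.75s) / (3 + 9 − 6.75s)

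| s | With team | Without team |
|---|---|---|
| 0 | 0/9 = 0% | 9/12 = 75% |
| 0.2 | 1.35/10.35 = 13% | 7.65/10.65 = 72% |
| 0.5 | 3.375/12.375 = 27% | 5.625/8.625 = 65% |
| 1 | 6.75/15.75 = 43% | 2.25/5.25 = 43% |

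The true rate is 9/21 = 43% in both groups. In this model the gap closes only when presence is counted for every caesarean labour to which the team was available. The protocol's attendance and handover rules do not secure that.

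**The case against.** The strongest defence is that the protocol does not plan this contrast as an analysis of the present study. The list is of potential outcomes for a trial, and the closing sentence promises the incidence of outcomes, not the comparisons. The analyses that are planned are descriptive and include mode of birth by intention to treat and by intended mode, which are free of this defect. All of that stands and limits the point to one line. It does not make the line sound.

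A reader might infer that the result is wholly fixed in advance. The documents do not support that, because vaginal and forceps breech are separate categories and can differ within actual vaginal breech births.

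A reader might also infer that caesareans must be counted as without the team. No such coding rule is stated, and an item that does not apply may simply be blank. Other sources exist: professionals present at birth (Secondary Outcomes, item 5), lead attendant under Labour Care, and, for randomised women, whether the lead attendant advised caesarean. These could reduce the bias. But presence at the birth is still affected by handover, the lead-attendant item is not stated to record proficiency, and the last item covers randomised women only.

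Figure 4, which defines the colours, is not available here, and green may denote a planned pathway. That would select Reading B over Reading A; it would not remove the problem.

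**Conclusion.** The point holds for the second mode-of-birth comparison under Cohort analysis. Under the actual-birth reading, the caesarean contrast is zero by definition. Under the planned-birth reading, grouping depends on the outcome and the bias favours the team.

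The amount of bias cannot be fixed from the documents. The 9/9 v 3/12 figure is an extreme that assumes every in-labour caesarean is coded as unattended and that the 12 births are vaginal breech births. The intermediate values further assume that availability is independent of mode. Adding the five pre-labour caesareans to the group without the team would widen the gap, but the text gives no ground for placing women who had no labour there. Significance tests on these counts would add nothing, since the planned analysis is descriptive.

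It would be wrong to carry this over to the randomised comparison of the two offers, the feasibility outcomes or the green/amber/red criteria. None of them uses this grouping.

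**What to change.** Choose one of three edits to Cohort analysis:

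1. Delete the second comparison for mode of birth and rely on the summaries by intention to treat and intended mode already listed under Statistical analysis. This is the simplest.
2. Redefine it among all women planning a vaginal breech birth when labour care starts, grouped by whether an OptiBreech lead was assigned or called at that point, whatever the final mode. Record the attendance and proficiency item under Labour Care for all labouring women. The result would still be observational: section 4 reports that lack of proficient attendance in OptiBreech 1 occurred at sites outside the randomisation pilot, so site and attendance are confounded.
3. Keep actual vaginal breech births as the groups, and limit the outcome to what can differ within them, such as use of forceps.

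The cost is one line of protocol text and, for the second option, moving one existing CRF item. No clinical rule changes.
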